### **Women's empowerment**

We will measure empowerment of MAGs through measuring agency using The Women's Agency Scale 61 (WAS-61) (Yount et al., 2020).

#### **Intrinsic agency**

We will assess women's intrinsic agency, using a validated, 29-item three-dimensional measure capturing women's intrinsic voice and mobility; gender equitable attitudes; and non-justification of wife beating (CFA standardized factor loadings: 0.54–0.81, 0.35–0.82, and 0.87–0.93, respectively; CFI = 0.94; TLI = 0.93; RMSEA = 0.04) (Yount et al., 2020).

Intrinsic voice and mobility will be measured using nine items capturing women's level of comfort (1 = not at all to 3 = very) going places alone, like the 'home of a relative', and expressing opinions with community members, like government officials, NGO officials, and community leaders. A summative score will be obtained, with a higher score indicating higher intrinsic voice and mobility.

Gender equitable attitudes will be measured using 14 items capturing women's agreement (1 = strongly disagree to 4 = strongly agree) with items, like "a woman should obey her husband," and "a couple should decide together if they want to have children." Negatively valenced items will be reverse-coded, so higher score indicates stronger endorsement of more equitable attitudes.

Non-justification of wife beating will be measured using six items capturing responses (1 = strongly disagree to 4 = strongly agree) to the question, 'Does a man have a good reason to hit his wife' if, for example, she 'disobeys him' or "rudely argues with him'. Items will be reverse-coded, so higher scores indicates stronger non-justification of wife beating.

#### **Instrumental agency**

We will assess women's instrumental agency using a validated, 17-item three-dimensional measure capturing women's use of financial services, voice with husband, and voice and mobility outside the home (CFA standardized loadings 0.57–0.95, 0.48–0.99, and 0.43–0.79, respectively, CFI = 0.94, TLI = 0.93, RMSEA = 0.05).

Five items will be used to measure women's frequency of using (1 = never to 4 = often) financial services, such as 'money deposit' and 'checking account'. A summative score will be obtained, with a higher score indicating more frequent use of financial services.

Three items will capture women's level of influence (1 = none to 4 = total) with their husband about 'how to spend money your husband gives you' and 'how to spend your husband's earnings' and their frequency of expressing opinions (1 = never to 4 = often) with husbands. A summative score will be obtained, with a higher score indicating higher level of influence with husband.

Nine items will be used to measure women's frequency (1 = never to 4 = often) of going places like 'the home of a relative' and expressing opinions with community members like government officials and community leaders. A summative score will be obtained, with a higher score indicating more frequent mobility and expressing opinions with community members.

#### **Collective agency**

We will assess women's collective agency regarding influence in the community using an eight-item validated scale (CFA standardized loadings 0.52–0.84; CFI = 0.96; TLI = 0.95; RMSEA = 0.10) and regarding women's leadership in groups using a validated seven-item scale (CFA standardized loadings: 0.54–0.83; CFI = 0.96; TLI = 0.95; RMSEA = 0.10). The participants will report their agreement (1 = totally disagree to 4 = totally agree) with statements like 'women like me can really understand what is going on with my community' and 'I am often a leader in groups', 'I prefer to be a leader rather than a follower', and 'Other people usually follow my ideas', etc. (Yount et al., 2020; Hinson et al., 2016). Summative scores will be obtained, with higher scores indicating stronger collective agency.

### **Critical Consciousness of MAGs related to their consent and choice in SRH**

Critical Consciousness (CC) is theorized to be composed of two subcomponents. One of them is critical reflection, which will encompass the ability to critically reflect on perceived societal inequalities as well as the endorsement of societal equality. The second component is critical action, which encompasses individual and/or collective action taken to change perceived social inequalities (Freire, 1993). We will measure critical consciousness of MAGs using the validated 15-item Critical Consciousness Scale (CCS) (Mandal et al., 2020). Ten critical reflection related items will be used to measure the perceived inequality and egalitarianism. A typical example include 'Women have fewer opportunities than men'. The response options include: strongly agree, agree, disagree and strongly disagree. Another five items will be used to assess critical action, or the degree to which they have participated in individual and/or collective action to produce sociopolitical change, with the response options – not at all, rarely, sometimes and often. A summative score will be obtained, with a higher score indicating higher critical consciousness.

### **Knowledge, attitudes, communication, negotiation and practices of MAGs regarding SRHR**

The MAGs will be asked about their knowledge, attitudes, practices, needs, consent, choice, communication and negotiation regarding FP use, conception and SRH service uptake. The questions will heavily draw upon the standard Demographic and Health Survey questionnaire (NIPORT & ICF, 2019), SAFE ([name] et al., 2018), IMAGINE and AdSEARCH FGWs Cohort questionnaires.

### **Knowledge of MAGs regarding FP and conception**

The MAGs knowledge on number of modern methods, and emergency contraceptive pill will be measured using two questions: i) which of the FP methods have you heard of; and ii) have you heard about emergency contraceptive pill. A continuous variable will be created for the first question based on the number of correct answers, while a binary variable will be created from the responses on the second question by recoding to '1=Yes' if the respondent heard of emergency contraceptive pill, and '0=No' otherwise.

The MAGs knowledge of regarding conception will be assessed using the following four questions: i) what is the appropriate age at first conception for a woman; ii) if a girl gets pregnant in her teenage years, what are the potential problems she might have to face; iii) after the birth of a child can a woman become pregnant before her menstrual period has returned; and iv) what are the consequences of not having proper spacing between two pregnancies. For questions i) and iii), separate binary variables will be created from the responses by recoding to '1=Yes' if it was a correct answer, and '0=No' otherwise. For questions ii) and iv), separate continuous variables will be created based on the number of correct answers.

A summative score will then be obtained by adding all the knowledge related variables, with a higher score indicating greater knowledge.

### **Positive attitudes of MAGs regarding FP and conception**

Positive attitudes of MAGs regarding SRHR will be measured using six items, like 'family planning is a women's business and a man should not worry' and 'a woman has right to choose when to first conceive'. The participants will report their agreement on a Likert scale (1 = strongly agree to 4 = strongly disagree). A summative score will be obtained, with a higher score indicating more positive attitude regarding SRHR.

### **Increase in couple communication initiated by MAGs regarding FP use, timing of first conception, and number of children to have**

The MAGs will be asked about any communication/discussion with husband regarding FP use, first conception, and number of children they want to have. The response options include "1=Yes" and "2=No". They will also be asked about who initiated the conversation, with the response options "1=herself", "2=husband" and "3=don't remember". Separate variables will be created from these responses by recoding

"herself" as "1"; "husband" as "0" and "don't remember" as "missing value". A summative score will be obtained by adding the number of conversations she initiated on different SRHR issues, with a higher score indicating higher initiated communication.

### **MAGs attempts to negotiate her choice of FP use, timing of first conception, and number of children to have**

The MAGs will be asked about what happened if there was any mismatch between her and her husband's choice regarding the above mentioned SRHR themes. We will assess if she attempted to negotiate in such case and also if her husband tried to convince her to accept his own choice. In both cases, an attempt to negotiate will be coded as '1', and '0' otherwise. A summative score will be obtained by accumulating the number of SRHR themes where she attempted to negotiate with a higher score indicating higher attempts.

### **Abortion and post-abortion service uptake and help seeking by physically and/or sexually abused MAGs**

If any MAG reports having an induced abortion/MR, she will be asked about venue of the service received, provider and the method of abortion. The MAGs with an abortion will be asked about post-abortion care. The MAGs who report experiencing any physical and/or sexual intimate partner violence will be asked about their help seeking. The results will be presented in frequencies and percentages.

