### Specific Objectives:

Describe the specific objectives of the proposed study. State the specific parameters, gender aspects, biological functions, rates, and processes that will be assessed by specific methods.

Primary objective:

- (1) To develop Balika Bodhu, a social norm intervention combining empowerment of MAGs and mobilisation of relevant stakeholders to promote demand for, access to, and practices of SRHR, including family planning (FP) use, conception, and SRH service uptake.
- (2) To measure the effect of Balika Bodhu in increasing demand for, access to and practices of SRHR (FP use, conception, and SRH service uptake) of MAGS.

Secondary objectives:

- (3) To measure the effect of Balika Bodhu on empowerment of MAGs;
- (4) To measure the effect of Balika Bodhu on social norm regarding SRHR of MAGs;
- (5) To explore how change happens or why change does not occur.

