| 8                         | Couple communication initiated by MAGs regarding FP use, timing of first conception, and number of children to have                      | √    |                  |                   |
| 9                         | MAGs attempts to negotiate FP use, timing of first conception, and number of children to have as per her choice                          | √    |                  |                   |
| 10                        | Service uptake among MAGs regarding abortion and post-abortion care, and help seeking after experiencing violence                        | √    |                  |                   |
| 11                        | Prevalence of intimate partner violence (IPV) among the MAGs                                                                             | √    |                  |                   |
| 12                        | Knowledge of husbands of MAGs regarding FP and conception                                                                                |      | √                |                   |
| 13                        | Positive attitudes of husbands of MAGs regarding FP and conception                                                                       |      | √                |                   |
| 14                        | Positive attitudes regarding agency of MAGs regarding SRHR among the husbands                                                            |      | √                |                   |
| 15                        | Non-condoning attitudes of husbands of MAGs regarding violence against women                                                             |      | √                |                   |
| 16                        | Positive attitudes of husbands of MAGs regarding gender roles within household                                                           |      | √                |                   |
| 17                        | Knowledge of community members regarding FP and conception                                                                               |      |                  | √                 |
| 18                        | Positive attitudes of community members regarding FP and conception                                                                      |      |                  | √                 |

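### Outcome 10 (service uptake and help seeking) is collected only from girls reporting an abortion or partner violence, so comparing those percentages between arms is not a randomised comparison, and the plan does not exclude it from the impact analysis

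*Protocol*

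**What the plan says.** Service uptake is one of three domains named in the protocol's hypothesis and in its second primary objective, beside family planning use and conception. Table 2 lists it as secondary outcome 10: "Service uptake among MAGs regarding abortion and post-abortion care, and help seeking after experiencing violence". The next row, outcome 11, is "Prevalence of intimate partner violence (IPV) among the MAGs".

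The measurement section for outcome 10 sets the filters. On abortion: "If any MAG reports having an induced abortion/MR, she will be asked about venue of the service received, provider and the method of abortion". On aftercare: "The MAGs with an abortion will be asked about post-abortion care". On violence: "The MAGs who report experiencing any physical and/or sexual intimate partner violence will be asked about their help seeking". It ends: "The results will be presented in frequencies and percentages". It names no denominator, no coding rule for girls without the event, and no recall period for the filters.

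Three other places bear on this:

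- *Study outcomes and measurement of study variables* says outcomes are measured once the intervention has been completed.
- *The Social Norm intervention* lists gender-based violence, anger and conflict management, contraception and unwanted pregnancy among the session topics.
- *Quantitative data analyses* says the impact on primary and secondary outcomes will be assessed by risk ratios or regression coefficients. The analysis is by intention to treat in all girls enrolled at baseline and interviewed at endline. Outcome 10 is not exempted.

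**The concern.** Randomisation makes the two sets of girls comparable. It does not make comparable the girls in each arm who later report violence or an abortion, if the programme changes who has or reports those events. For violence this is the programme's evident aim: it is a separate outcome and a session topic. For abortion it is plausible through the contraception and unwanted-pregnancy content, though the protocol does not state it as an aim.

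Suppose the programme mainly prevents milder violence. The girls left in the subgroup then have more severe experiences and, if severity drives help seeking, a higher percentage seek help. If the programme instead makes girls readier to report milder acts, the percentage falls. A risk ratio computed in the subgroup could present either shift as an effect on service uptake, which is a domain of a primary objective. Nor can a question put only to a subgroup deliver the promised analysis of all girls interviewed unless the others are coded.

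**Working it through.** **The protocol's own figure.** The sample size section gives 50% against 65% (a 15-point effect), 5% significance, 80% power, intra-cluster correlation 0.05 and 22 girls per cluster. The standard two-proportion formula (two-sided, no continuity correction) gives 170 per arm. The design effect is 1 + (22 − 1) × 0.05 = 2.05. Then 170 × 2.05 = 348.5, and 348.5 / 22 = 15.84, rounded up to the stated 16 clusters per arm. The design number at endline is therefore 16 × 22 = 352 girls per arm. The protocol gives no figure for outcome 10.

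**Passages side by side.** The measurement section fixes who is asked and mentions only frequencies and percentages. The analysis section applies effect estimation to every secondary outcome. Read together, they allow a risk ratio among girls with the event.

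**Illustration. All rates are assumed; none is in the protocol.** In the control arm 30% of girls have milder and 10% severe physical or sexual violence. The probability of seeking help is 5% after milder and 30% after severe violence, *the same in both arms*. With m and s the milder and severe prevalences:

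- help seeking among abused girls = (0.05m + 0.30s) / (m + s)
- event with help, all girls = 0.05m + 0.30s
- event without help, all girls = (m + s) − (0.05m + 0.30s)

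Control: (0.015 + 0.030) / 0.40 = 11.25%.

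| Intervention arm | Violence, all girls (%) | Help among abused (%) | Ratio to control | With help, all girls (%) | Without help, all girls (%) |
|---|---|---|---|---|---|
| Same as control | 40.0 | 11.25 | 1.00 | 4.5 | 35.5 |
| Milder falls 25% | 32.5 | 12.69 | 1.13 | 4.125 | 28.375 |
| Milder falls 50% | 25.0 | 15.00 | 1.33 | 3.75 | 21.25 |
| Both fall 50% | 20.0 | 11.25 | 1.00 | 2.25 | 17.75 |
| Only severe falls 50% | 35.0 | 8.57 | 0.76 | 3.0 | 32.0 |
| Reported milder rises 50% | 55.0 | 9.55 | 0.85 | 5.25 | 49.75 |

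If help seeking does not vary with severity (15% in both strata), halving milder violence leaves the percentage at 15% in both arms, a ratio of 1.00.

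Two things follow. The subgroup ratio moves in either direction, or not at all, with help seeking held fixed. The all-girl columns keep the randomised arms but move too: when milder violence halves, event without help falls from 35.5% to 21.25% purely because there is less violence.

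**Subgroup size and noise.** In the third row the subgroups hold 352 × 0.40 = 141 and 352 × 0.25 = 88 girls. The spurious difference is 3.75 points. Its standard error before clustering is √(0.1125 × 0.8875/140.8 + 0.15 × 0.85/88) = 4.6 points, so z is about 0.8. At an assumed abortion rate of 2% to 5%, the abortion subgroup is 352 × 0.02 = 7 to 352 × 0.05 = 18 girls per arm.

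**The case against.** The strongest reply is that the protocol never plans this comparison. The measurement section says only "The results will be presented in frequencies and percentages", whereas most other outcomes for the girls get a score or a coding rule. That supports a descriptive reading, and a skip pattern is not a denominator, which could be left to an analysis plan. This stands in part: the descriptive reading is available. But the general sentence in the analysis section covers all secondary outcomes, so the two sections conflict and the protocol does not settle which governs.

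A reader might infer several stronger points that the text does not support:

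- *The programme is meant to reduce both events.* This is well supported for violence. For abortion it is only an inference from session content.
- *Averted violence counts for nothing.* It counts in outcome 11.
- *Uptake will appear to rise.* The direction is not fixed, and even the largest upward shift illustrated would be well inside sampling error in a trial of this size.
- *The trial can say nothing on service uptake.* The protocol also plans questions on practices, choice and negotiation regarding service uptake, and norms about it enter outcome 22. These do not, however, add another listed uptake outcome.

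The recall period also matters. The physical-violence example item asks about lifetime experience. If the help-seeking filter does the same, part of the subgroup was fixed before randomisation. That dilutes the bias without removing it.

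**Conclusion.** The concern holds in a limited form. Outcome 10 is observed only in subgroups defined by events reported after the intervention. One of those events is another trial outcome, and the analysis section would estimate effects on outcome 10 as on every secondary outcome. A within-subgroup comparison is not a randomised one. Its size cannot be derived from the protocol. Under the assumed rates the ratio runs from about 0.76 to 1.33 with no change in help seeking, and is 1.00 when milder and severe violence fall equally or when help seeking does not depend on severity.

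It is tempting to conclude that the share of all girls with violence and no help should replace outcome 10. It should not: in the illustration that share improves although help seeking is unchanged, so it cannot stand alone as service uptake. The point concerns one secondary outcome, and the primary outcome is unaffected. It matters because service uptake is named in a primary objective and outcome 10 is the only listed outcome that measures it.

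**What to change.** Reconcile the two sections. State that percentages among girls with an abortion or with violence are descriptive, are not effect estimates, and are excluded from the impact analysis in *Quantitative data analyses*.

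For any between-arm estimate, use all girls interviewed at endline as the denominator, with a post-baseline reference period and girls without the event coded as no. Report by arm, side by side, separately for violence and for abortion: occurrence of the event, event with help or care, and event without help or care. State that event without care is not to be read alone as service uptake, and that the trial's conclusion on service uptake is limited accordingly.

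The cost is small: a reference period on questions already planned, a coding rule, a few table rows and two sentences of text. The downside is that the all-girl figures mix occurrence with care, so none of them isolates a change in help seeking.

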### **Intimate partner violence (IPV)**

MAGs' experience of IPV (i.e. controlling behaviour, and physical and sexual violence IPV) will be measured using a modified version of The Revised Conflict Tactic Scale (Straus et al., 1996). The scale is the most widely used measure of IPV which is characterized by having direct and behaviorally explicit questions in order to reduce variation in the interpretation and understanding of what violence comprises of. These instruments are designed to minimize reporting biases that arise from subjective perceptions of abuse by asking only about specific behaviours perpetrated by a male partner (e.g., "Has your husband or any other family member ever slapped you or threw something at you that could hurt you?"). Questions will capture behaviours that reflect minor and severe physical violence (e.g., slapped, pushed, hit with a fist, kicked, dragged, choked, burned, threatened with a weapon); and sexual violence (e.g., forced sexual intercourse or other sexual acts). To measure economic coercion, we will use a modified version of the ECS-20 (Yount et al., 2022). Typical items include—your husband or any other family member ever and in last 12 months: disallowed you to go to your work, school or training, or do any home-based income earning activity; told that you could work outside the home only if you kept up with the housework; told that you could earn income only if you worked from home; etc. A woman will be considered exposed to any specific type of IPV if she responds "yes" to any of the items related to that specific type of IPV, and will be coded "yes=1", and "no=0" otherwise.

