## The Social Norm intervention

In line with the ToC the Balika Bodhu intervention will be developed heavily drawing on CARE's IMAGINE model (CARE, 2019), and on SAFE, a project spearheaded by icddr,b and aimed at promoting SRHR and addressing violence against women in slums of Dhaka ([name] et al., 2018).

Balika Bodhu intervention will be implemented by Nari Maitree, an NGO working on women's issues. The research team will conduct both quantitative and qualitative monitoring for documenting implementation fidelity. This will allow tracking of any deviations from the charted programme, which will be important to take into consideration during interpretation of the results. Effectiveness of the intervention will be assessed in changing social norms endorsing denial of SRHR to MAGs and in empowering them to demand, access and practice SRHR. The intervention will involve a 12-month gender transformative participatory programming for: (1) empowering MAGs and (2) creating an enabling environment in the family and the community for the MAGs to demand, access and practice SRHR. For empowering MAGs their intrinsic, instrumental and collective agency will be promoted. Special attention will be paid to incorporate two critical elements, often missing from many empowerment programmes – development of critical consciousness and movement building. The intervention will particularly focus on promoting rights of the MAGs through enhancement and exercise of the notions of choice and consent.

The intervention will target Married adolescent girls, their spouses, and elderly/influential community members. Thirty-six 2-hour weekly sessions will be conducted with MAGs. The session topics will be categorized into two broad headings: i) Health and life skills sessions covering, for example topics such as sex and gender, rights, marriages, SRHR (e.g., first conception, birth spacing, contraception, healthy relationships, polygamy, divorce, gender-based violence (GBV), communication and negotiation, anger and conflict management, goal setting, household budgeting, activism, leadership skills, and community action planning, and ii) Business and entrepreneurship sessions, which will basically include sessions smart planning of businesses (e.g., market research, business planning, and adding value).

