Spouses of the MAGs will receive 20 2-hour bi-weekly sessions. The session topics will cover: sex and gender, rights, marriages, registration, dowry, conception and contraception, healthy relationships, polygamy, divorce, gender-based violence (GBV), communication and negotiation, anger and conflict management, goal setting, and household budgeting.

A total of three 2-hour couples sessions will be held, each to be delivered every two months, starting from the 6th month of the intervention. The session topics will include teenage pregnancy, unwanted pregnancy, and action planning. Elderly and influential community members will have three 2-hour bi-monthly sessions starting from the 6th month of the intervention, covering topics related to teenage pregnancy, unwanted pregnancy, and action planning.

MAGs with leadership qualities will be identified and trained to conduct campaigns and activism. They will be put in contact with other girls' groups and networks, mentored and given access to resources to execute at least two community-level social norm activities. These leaders will also receive training on income generating.

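### The intimate partner violence outcome is described as male-partner only, but its physical-violence example and economic-coercion items count acts by any family member

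*Protocol*

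**What the plan says.** Table 2 of the Protocol lists outcome 11, a secondary outcome measured among the girls, as "Prevalence of intimate partner violence (IPV) among the MAGs".

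The section Intimate partner violence (IPV) says the instruments limit reporting bias by "asking only about specific behaviours perpetrated by a male partner". The example attached to that same sentence is "Has your husband or any other family member ever slapped you or threw something at you that could hurt you". The economic-coercion items are introduced with "your husband or any other family member ever and in last 12 months".

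The coding rule is "A woman will be considered exposed to any specific type of IPV if she responds 'yes' to any of the items". The sentence goes on to limit the items to those of the type concerned, so there is one yes/no variable per type of IPV. The section describes no question or variable that identifies the perpetrator.

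On content, the section The Social Norm intervention says "The intervention will target Married adolescent girls, their spouses, and elderly/influential community members". The husbands' sessions include "gender-based violence (GBV), communication and negotiation, anger and conflict management, goal setting, and household budgeting", and the girls' sessions also cover gender-based violence and anger and conflict management. The couples' and community sessions list teenage pregnancy, unwanted pregnancy and action planning.

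The section on help seeking says "The MAGs who report experiencing any physical and/or sexual intimate partner violence will be asked about their help seeking".

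**The concern.** The name and stated scope of outcome 11 are narrower than the items it is built from. A girl slapped by a mother-in-law or brother-in-law, and never by her husband, answers yes truthfully and is coded as exposed to physical IPV.

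Two things are at stake. First, the reported prevalence would be that of violence by a husband or any relative, under the label of partner violence. Second, the between-arm contrast would merge an effect on husbands, who receive sessions on violence, with behaviour of other relatives, for whom the plan lists no violence content. A weak result could then mean that husbands did not change, or that they changed while other relatives did not. The data as described could not tell these apart.

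**Working it through.** **Definition, items and coding side by side**

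| Element | Perpetrator covered |
|---|---|
| Outcome name (Table 2, outcome 11) | Intimate partner |
| Stated scope of the instruments | Male partner only |
| Physical-violence example | Husband or any other family member |
| Economic-coercion stem | Husband or any other family member |
| Coding rule | Any yes within a type; no perpetrator split |
| Sexual-violence and controlling-behaviour stems | Not shown |

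The first two rows contradict the next two. Because any single yes suffices, one physical item with the wider stem is enough to widen the whole physical-violence variable. The contradiction needs no arithmetic.

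**Possible size: illustration only**

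The protocol gives no figure for violence by husbands or by other relatives, so every rate below is assumed. Let *h* be the proportion of girls harmed by the husband and *q* the proportion harmed by another relative. Assume the two are independent and *q* is the same in both arms.

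- Measured proportion = 1 − (1 − *h*)(1 − *q*)
- Measured difference between arms = (1 − *q*) × (true difference in *h*)

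Take *h* = 25% in control and 18% in intervention, so the true risk ratio is 0.18/0.25 = 0.72:

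| *q* | Control | Intervention | Risk ratio |
|---|---|---|---|
| 5% | 1 − 0.75 × 0.95 = 28.8% | 1 − 0.82 × 0.95 = 22.1% | 0.77 |
| 10% | 32.5% | 26.2% | 0.81 |
| 15% | 36.3% | 30.3% | 0.84 |
| 20% | 40.0% | 34.4% | 0.86 |

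The only design figure in the protocol is 16 clusters per arm, set for the primary outcome. It reproduces. A comparison of 50% with 65% at two-sided 5% and 80% power needs 170 girls per arm. The design effect is 1 + 21 × 0.05 = 2.05, and 170 × 2.05 / 22 = 15.84, rounded up to 16. The effective number per arm is 16 × 22 / 2.05 = 171.7.

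Carrying that base rate and a 15-point effect over to husbands' violence (50% against 35%, again assumed) gives:

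| *q* | Measured difference (points) | Risk ratio | Power |
|---|---|---|---|
| 0% | 15.0 | 0.70 | 81% |
| 5% | 14.3 | 0.73 | 76% |
| 10% | 13.5 | 0.76 | 71% |
| 20% | 12.0 | 0.80 | 61% |
| 30% | 10.5 | 0.84 | 51% |

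Independence matters here. If *a* is the share also harmed by another relative among girls whose husbands' violence the programme prevents, the measured difference is (1 − *a*) times the true one. Independence sets *a* = *q*. With *a* = 0 the absolute difference is intact, although the prevalence is still overstated and the risk ratio still moves towards 1. The protocol does not inform *a*.

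**The case against.** The strongest reply is that this is a drafting inconsistency in one of 21 secondary outcomes. The section gives examples rather than the instrument. The questionnaire is not at hand, and the protocol says it is still to be developed, pre-tested and piloted. The protocol also speaks of domestic violence elsewhere (key words, abbreviations, Table 1, the ethics sections), so a family-wide measure may be intended and only the label wrong. That possibility stands and is why relabelling is offered below. It does not remove the contradiction between stated scope, items and coding.

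Several stronger readings are tempting, and the document does not support them.

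- **That the outcome fails to measure partner violence at all.** Husbands' violence is inside both stems shown. What is lost is specificity.
- **That misclassification will be common because most girls live with husbands and in-laws.** The same part of Ethical considerations calls husbands the most common perpetrators, and only girls harmed by a relative and not by the husband are misclassified.
- **That nothing can be done at analysis.** A perpetrator follow-up question cannot be excluded. If one exists, the stated coding rule ignores it and needs only rewording.
- **That all IPV is affected.** The wider stem is shown for one physical item and for economic coercion. Moreover, the section's opening list of IPV types names controlling, physical and sexual forms, so the standing of economic coercion as an IPV type is itself unclear.
- **That the programme does not reach other relatives.** This is an inference from session lists. The protocol states a family-level aim, plans community norm activities, and some in-laws may attend as elderly or influential community members.
- **That the dilution figures estimate a real loss.** They rest wholly on assumed rates. The physical item also asks about lifetime experience in girls who are followed over time. Exposure already reported at baseline cannot fall, so a simple endline contrast is a rough model for it.
- **That help seeking should be limited to husband-perpetrated violence.** Outcome 10 refers to help seeking after violence, without restriction to partners, and its section heading refers to physically or sexually abused girls.

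**Conclusion.** The concern holds in a limited form. The IPV section contradicts itself on whose acts count. Followed as written, it would report violence by a husband or any other family member as IPV, for physical violence and economic coercion at least. An effect on husbands' violence could not be isolated within those variables.

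This conclusion rests on the two stems shown, the any-yes rule and the absence of a described perpetrator variable. It assumes that the questionnaire follows the section. The size of the mixing is unknown and may be modest. The primary outcome is not affected. The point is worth correcting because it decides what a named trial outcome means and the correction is small.

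**What to change.** Reconcile definition, items and coding in the IPV section:

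1. For each violence and economic-coercion item, record the perpetrator as husband, other family member, or both.
2. Code each type of IPV in outcome 11 as 1 only when the husband is a perpetrator.
3. Report violence by other family members as a separate domestic-violence variable.
4. If perpetrators are not recorded, rename outcome 11 as domestic violence by husband or family, and drop the statement that only a male partner's acts are asked about.
5. Keep help seeking for all physically and/or sexually abused girls, in line with how outcome 10 is named, and report it by perpetrator. The entry condition in the help-seeking section needs matching wording. Otherwise husband-only coding would remove girls abused only by other relatives.

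The cost is one extra response field per item on the tablet, a slightly longer interview and a revised coding rule, with no additional participants. The reported IPV prevalence will be lower than under the wider stem.
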